#### Objective 2: Measure of Technology Acceptance and Usability

The UTAUT questionnaires measure performance expectancy, effort expectancy, social influence, and facilitating conditions, and behavioral intention with respect to 3MDR and the CAREN [56]. Differences in the medians between groups (ie, performance expectancy, effort expectancy, social influence, and facilitating conditions, and the behavioral intention responses of intervention and control groups) will be analyzed by nonparametric tests. Acceptance will be assessed using the PLS structural equation model to determine reliability measurements for each construct (Cronbach α).

#### Objective 3: 3MDR Operators and Clinicians

Owing to the small anticipated sample size, nonparametric statistical analysis with the Wilcoxon signed-rank test will be employed to assess the outcome measures addressing clinician and operator stress. Qualitative interviews will be thematically analyzed as described above.

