**Methods:**

This is a mixed-methods waitlist controlled crossover design randomized controlled trial. Participants include both CAF-SMs and veterans (N=40) aged 18-60 years with combat-related TR-PTSD (unsuccessful experience of at least 2 evidence-based trauma treatments). Participants will also include clinicians and operators (N=12) who have been trained in 3MDR and subsequently utilized this intervention with patients. CAF-SMs and veterans will receive 6 weekly 90-minute 3MDR sessions. Quantitative and qualitative data will be collected at baseline and at 1, 3, and 6 months postintervention. Quantitative data collection will include multiomic biomarkers (ie, blood and salivary proteomic and genomic profiles of neuroendocrine, immune-inflammatory mediators, and microRNA), eye tracking, electroencephalography, and physiological data. Data from outcome measures will capture self-reported symptoms of PTSD, moral injury, resilience, and technology acceptance and usability. Qualitative data will be collected from audiovisual recordings of 3MDR sessions and semistructured interviews. Data analysis will include univariate and multivariate approaches, and thematic analysis of treatment sessions and interviews. Machine learning analysis will be included to develop models for the prediction of diagnosis, symptom severity, and treatment outcomes.

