### Hypotheses

Related to the objectives above, we have derived the following four hypotheses for this study.

Hypothesis 1: Participants’ symptoms of combat-related TR-PTSD will decrease during the 3DMR therapy compared with treatment as usual.

Hypothesis 2: CAF-SMs, veterans, 3MDR clinicians, and operators will perceive 3MDR to be a novel intervention with adequate perceived technology acceptance and usability.

Hypothesis 3: 3MDR operators and clinicians will not experience adverse mental health effects, including secondary trauma and stress, that affect their daily functioning as a result of 3MDR delivery.

Hypothesis 4: Machine-learning analysis will generate two accurate predictive models that may portend diagnosis, severity, and potential treatment outcomes in CAF-SMs and veterans with combat-related TR-PTSD.

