Recruitment of 3MDR clinicians and operators (N=12) will be conducted through word of mouth among the six international 3MDR research teams located in the Netherlands, the United States (California and Maryland), the United Kingdom (Wales), and Canada (Alberta and Ontario). Clinicians and operators who have received training for 3MDR and completed 6 weeks of interventions will be eligible for a pre/post evaluation. Voluntary written informed consent will be obtained from all participants.

The control group will undergo screening for eligibility and baseline assessment, followed by 9 weeks of treatment as usual while the intervention group receives the 3MDR intervention. They will then be provided an opportunity to cross over into the intervention group.

For the introductory session, intervention group participants will become accustomed to the CAREN system by practicing the process associated with 3MDR, including walking on the treadmill while looking at a neutral image as the clinician guides them through the 3MDR protocol. The participant will be asked to provide (1) images reminiscent of the traumatic deployment event that preceded a PTSD diagnosis, ranked according to the emotional distress that each elicits (ie, from least to greatest level of distress); and (2) digital music tracks of a song that reminds them of their deployment and other sounds or music that provide positive feelings. A secondary purpose of this introductory session is also to transfer trust from their service provider to the 3MDR researchers and clinicians. One week after the introductory session, the 3MDR therapy will be initiated and participants will undergo 6 90-minute sessions.

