#### Objective 3: 3MDR Operators and Clinicians

The impact of delivering 3MDR will be examined with clinicians and operators using questionnaires related to technological acceptance, perceived stress, and professional quality of life prior to 3MDR training and on completion of a full course of 3MDR with a study participant (Table 2).

**Table 2 table2:** Time points of data collection for multimodular motion-assisted memory desensitization and reconsolidation (3MDR) clinicians and operators.

Construct to be measured	Measure	Week 1 (Baseline)	Week 9 (Post)
Technology Acceptance and Usability	UTAUT^a^ Questionnaire	X	X
Perceived Stress	PSS^b^	X	X
	SUDS^c^	X	X
	Subjective Interview		X
Professional Quality of Life	PQoL^d^	X	X
Secondary Stress	STSS^e^	X	X

^a^UTAUT: Unified Theory of Acceptance and Usability of Technology.

^b^PSS: Perceived Stress Scale.

^c^SUDS: Subjective Units of Distress Scale.

^d^PQoL: Professional Quality of Life Scale.

^e^STSS: Secondary Traumatic Stress Scale.

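### Hypothesis 3 predicts no functionally important harm to staff, but a difference test in about 12 people who completed delivery cannot establish that

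*Protocol article*

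**What the plan says.** Under Hypotheses, the protocol article predicts that "3MDR operators and clinicians will not experience adverse mental health effects, including secondary trauma and stress, that affect their daily functioning" because of delivering 3MDR.

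Under Data Analysis, Objective 3, the test is chosen "Owing to the small anticipated sample size", and "nonparametric statistical analysis with the Wilcoxon signed-rank test will be employed to assess the outcome measures addressing clinician and operator stress". Interviews are analysed thematically alongside it.

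The number is fixed under Recruitment: "Recruitment of 3MDR clinicians and operators (N=12) will be conducted through word of mouth", among six international 3MDR teams. No effect size or precision target is attached to it.

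Three places describe who is evaluated and when:

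- Recruitment: "Clinicians and operators who have received training for 3MDR and completed 6 weeks of interventions will be eligible for a pre/post evaluation".
- Abstract, Methods: "clinicians and operators (N=12) who have been trained in 3MDR and subsequently utilized this intervention with patients".
- Study Timeline and Data Collection, Objective 3: questionnaires are given "prior to 3MDR training and on completion of a full course of 3MDR with a study participant". Table 2 labels these two points Week 1 and Week 9. It lists the PSS, SUDS, professional quality of life scale and STSS at both, and the interview at Week 9 only.

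**The concern.** There are two separate problems, and both tilt the result towards finding nothing.

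First, the hypothesis is one of absence, while the test is built to detect presence. With few people, a non-significant result is likely whether or not staff are moderately worse off.

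Second, entry to the pre/post evaluation depends on having completed delivery. A clinician or operator who began and then withdrew because the work was distressing is among the most informative people for this question, and is the one left out.

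At stake is the answer to research question 5, whether delivering 3MDR brings secondary traumatic stress or a change in professional quality of life.

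**Working it through.** **Inputs.** From the article: N=12 (Abstract; Recruitment); Wilcoxon signed-rank test on paired pre/post scores (Data Analysis, Objective 3). Two-sided 0.05 is stated under Objective 1 and assumed to carry over. The article gives no effect size or SD for this objective, so the standardised shift d = (mean change)/(SD of the change scores) is an assumption, shown over a range with normally distributed changes. N=12 comes with no inputs, so there is no plan figure to reproduce.

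**Step 1: power of the stated test.** The critical values come from the exact null distribution. At n=12 the two-sided test rejects when the smaller rank sum is 13 or less (attained level 2 × 0.0212 = 0.042). Power was simulated with 100,000 replicates.

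| Assumed worsening d | 0.2 | 0.3 | 0.5 | 0.8 | 1.0 |
|---|---|---|---|---|---|
| Power, two-sided | 0.08 | 0.14 | 0.32 | 0.67 | 0.85 |
| Power, one-sided 0.05 | 0.15 | 0.23 | 0.46 | 0.80 | 0.93 |

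A true worsening of d=0.5 is therefore missed about 1 − 0.32 = 68% of the time two-sided, or 54% one-sided. The smallest shift detectable with 80% power is about 0.93 two-sided and 0.80 one-sided. Detecting d=0.5 with 80% power needs about 36 people (34 for the paired t-test, divided by 0.955).

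**Step 2: units.** A shift of 0.5 in raw-score SDs converts as d = 0.5/√(2(1 − r)), where r is the pre/post correlation (assumed).

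- r=0.5: d=0.50, power 0.32.
- r=0.7: d=0.5/√0.6=0.65, power about 0.48.
- r=0.8: d=0.5/√0.4=0.79, power about 0.66.

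**Step 3: precision if the observed mean change is zero.** The half-width is t/√n, in SDs of change.

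- Two-sided 95%: 2.201/√12 = 0.64.
- One-sided 95% bound: 1.796/√12 = 0.52.

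On either scale an observed change of nil leaves a worsening of 0.5 SD of change inside the limit.

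**Step 4: what 12 people could establish.** Take an assumed harmful margin of 0.5 SD of change and a true change of zero. Power to exclude the margin (noncentral t, 11 df, noncentrality 0.5√12 = 1.73) is 0.35 at one-sided 0.025 and 0.49 at one-sided 0.05. For 80% power, n = ((z(1−α) + z(0.80))/0.5)², which gives 32 and 25.

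**Step 5: who is in the analysis.** There are two readings of Recruitment and the Objective 3 timeline.

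- Literal: a person becomes eligible only after training and six weeks of delivery. A baseline before training cannot then be collected prospectively from that person.
- Charitable: baselines are taken early, and Recruitment only defines who enters the paired comparison. The timing then fits.

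On both readings, staff who start and stop do not enter the pre/post comparison. The interviews are scheduled only at Week 9, after delivery, so they do not clearly reach these people.

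**The case against.** The strongest reply is that nothing in the article says a non-significant P value will be taken to confirm Hypothesis 3. That is right. Research question 5 and the third objective are worded neutrally, and a paired test does address whether scores change. A reader might infer that the plan will declare staff safe on a null P; the text does not go that far. A margin or decision rule could also sit in a fuller document, so its absence here is not the point. What stands is that this hypothesis, test, number and eligibility rule are fixed in the article and do not fit together.

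Other replies carry partial weight:

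- The hypothesis concerns harm that affects daily functioning, not any shift in scores, and the interviews bear on it. They add evidence, but from people measured after delivery.
- The eligibility and baseline passages can be read together, as Step 5 shows, so calling them flatly incompatible is too strong. The exclusion of those who stop remains. No staff member is reported to have stopped because of distress.
- The power figures use SDs of change and a two-sided test. A one-sided view, or a high pre/post correlation, raises them. There are also four quantitative scales, and missing harm on one is not missing it on all. The 68% is thus a figure for one scale under stated assumptions, not a general miss rate.
- The nine staff reported under Results are interim accrual, and some may have given only an interview. The planned 12 is the right basis for the calculation.
- One might infer that the staff result would be used to justify wider roll-out. The article ties wider access to 3MDR being effective and says the results will inform a full-scale trial, so this is not supported.

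**Conclusion.** The point holds in limited form. A Wilcoxon test in about 12 people cannot support a conclusion of no harm: power is about 0.32 at 0.5 SD of change and 0.67 at 0.8 SD, and an observed change of zero would still be compatible with a worsening of up to 0.64 SD (0.52 with a one-sided bound). These figures assume normal changes, no dropout among the 12, and shifts chosen for illustration because the article gives none. The mismatch between a hypothesis of absence and a test of difference does not depend on the exact shift. The completers-only rule survives both readings of the text and needs no arithmetic.

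This is a secondary staff objective. It should be corrected, but it does not touch the patient comparison.

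**What to change.** 1. Reconcile Recruitment with the Objective 3 timeline. Enrol clinicians and operators still to be recruited before training, and include or account for everyone who starts delivery, including those who stop.
2. For staff already enrolled, who cannot be given a new baseline, report how many were trained, started and stopped.
3. Report change on the STSS, PSS and professional quality of life scale with 95% confidence intervals, beside the interview findings.
4. Choose one of two stances in advance. Either conclude no adverse effect only if the interval excludes a pre-stated harmful change and otherwise call the result inconclusive, or label Objective 3 descriptive and draw no conclusion of no harm.

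The cost is revised wording, earlier consent across the participating teams, and some follow-up of staff who stop. No larger sample is required. The downside is that with 12 people the quantitative result will probably be inconclusive, since the power to exclude 0.5 SD of change is only 0.35 to 0.49.

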#### Objective 4: Machine Learning

In a supervised regression learning approach, the input of the machine-learning pipeline is considered to be the various types of data collected for each individual across every session. If the performance task is predicting reductions in symptom severity, then the output will contain psychological outcome measures. Such data will be divided into training and testing examples, whereby the statistical model will learn on the training set and then make data-driven predictions on the testing set to gauge how accurate those predictions were. During this process, the learner will optimize its predictions by comparing the predicted output with the observed output and then updating the parameters based on the severity of the errors made. Ultimately, the learned model will make individualized predictions about how a patient may respond to the treatment of 3MDR at a given time point.

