### Sample Size

A sample size calculation was conducted using G*Power 3 [55], based on the primary hypothesis that 3MDR would result in significantly lower clinician-rated PTSD symptoms as compared to treatment as usual. To detect a significant interaction with at least a medium effect size, a minimal sample size of 17 participants was determined for each group. Because of an estimated 10% dropout and some attrition at measurements, the sample size was set at 20 participants in each group (Cohen f=1.0) using general linear modeling with one within-subjects factor (2 time points) and one between-subjects factor (2 interventions), and assuming a correlation of r=0.5 between the repeated measures, an α-level of .05, and a power (1 – β) of 0.8.

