#### Objective 4: Machine Learning

Although group-based statistical analysis is useful for drawing conclusions about general trends, it has limited utility for guiding individual diagnostic and treatment choices.

As a result, in addition to conventional statistical analysis, this study will explore the application of machine learning in an attempt to identify individual data patterns that may predict diagnosis, severity, and potential treatment outcomes. Physiological, biometric, biological, and qualitative data from T0 to T3 will be used to predict psychological outcome measures at week 9 plus follow-up sessions. A model that can compute sequential, multimodal data is needed to autonomously observe and learn the variability of the relevant feature sets and its association with outcome measures [57,58]. Deep neural networks will be applied for this task [57,58].

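### Hypothesis 4 predicts accurate models, but a training/testing division of at most 40 people with no comparator cannot show whether a deep network adds anything to a baseline score

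*Protocol article*

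**What the plan says.** Hypothesis 4 reads "Machine-learning analysis will generate two accurate predictive models that may portend diagnosis, severity, and potential treatment outcomes". In Study Timeline and Data Collection, Objective 4 names the learner, "Deep neural networks will be applied for this task", and frames the aim as exploration: "this study will explore the application of machine learning in an attempt to identify individual data patterns".

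The two Objective 4 sections describe the inputs differently. The data-collection section says "Physiological, biometric, biological, and qualitative data from T0 to T3 will be used to predict psychological outcome measures at week 9 plus follow-up sessions" and does not list the psychological scales as predictors. The Data Analysis section takes as input "the various types of data collected for each individual across every session", which is broad enough to include them. The Discussion (Projected Outcomes) also names symptom severity among the bases of the models.

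On validation, the Data Analysis section says "Such data will be divided into training and testing examples, whereby the statistical model will learn on the training set" and that the model will then "make data-driven predictions on the testing set to gauge how accurate those predictions were". It names no benchmark. The same article does specify resampling for the biomarker models under Objective 1: leave-two-out for the PLS correlation and 5000 bootstrap iterations for the loadings.

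The trial plans 20 + 20 = 40 patients. The Sample Size section works by "assuming a correlation of r=0.5 between the repeated measures".

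**The concern.** Two weaknesses combine.

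- **Precision.** A hold-out from 40 people leaves very few test cases, so the accuracy figure depends largely on who falls into the test set.
- **Reference point.** Repeated measures of symptom severity are correlated. A simple regression on the starting score therefore predicts later severity to some extent, with no contribution from EEG, eye tracking, biomarkers or session recordings. Accuracy judged in isolation cannot separate that from real added value.

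At stake is what Hypothesis 4 can conclude. The Discussion looks ahead to models that support treatment decisions for individual clients. The described evaluation could neither support nor refute the idea that the network does better than a baseline questionnaire. The primary treatment comparison is not affected.

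**Working it through.** **Inputs from the article.** 40 patients at most; planning correlation r = 0.5; α = .05; power 0.8; 10% dropout. **Assumptions.** 20-30% of participants held out, division by person, and equal variances at the two time points. The article states none of these.

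**1. The plan's own figure.** Objective 4 has no sample size of its own; the trial's comes from the primary hypothesis. For a repeated-measures interaction with 2 groups and 2 times, λ = f²·N·2/(1 − r). Taking medium as f = 0.25 (by convention) and N = 34:
- λ = 0.0625 × 34 × 2 / 0.5 = 8.5, with 1 and 32 degrees of freedom. Power is 0.807, so 17 per group reproduces.
- 17/0.9 = 18.9, rounded up to 19 and set at 20.

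The printed f = 1.0 does not give 17 per group. That is a separate matter; here it matters only that r = 0.5 belongs to a calculation that otherwise reproduces.

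**2. Size of the test set.** 0.2 × 40 = 8 and 0.3 × 40 = 12. If only 34 people have usable data, the test set is 7 to 10.

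**3. Precision of the test-set correlation.** One split was simulated 8,000 times per setting, with a single predictor truly correlated 0.5 with the endpoint score.

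| Test people | Median r | 95% range of r | Median test R² | 95% range of R² | r above 0.5 | r above 0.7 |
|---|---|---|---|---|---|---|
| 8 | 0.53 | -0.28 to 0.90 | 0.22 | -0.82 to 0.67 | 55% | 26% |
| 12 | 0.52 | -0.11 to 0.84 | 0.21 | -0.53 to 0.60 | 53% | 18% |

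Fisher's formula, tanh(atanh 0.5 ± 1.96/√(n − 3)), agrees: -0.32 to 0.89 at n = 8 and -0.10 to 0.83 at n = 12.

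**4. A worthless model.** With true correlation zero, t = r√(n − 2)/√(1 − r²). At r = 0.5:
- n = 8: t = 0.5 × √6/√0.75 = 1.41 on 6 df, so P(r ≥ 0.5) = 0.104.
- n = 12: t = 0.5 × √10/√0.75 = 1.83 on 10 df, so P(r ≥ 0.5) = 0.049.

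**5. What baseline severity alone explains.** For the endpoint score R² = r². For the change score the correlation with baseline is -√((1 − r)/2), so R² = (1 − r)/2.

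| r | R², endpoint | R², change |
|---|---|---|
| 0.3 | 0.09 | 0.35 |
| 0.5 | 0.25 | 0.25 |
| 0.7 | 0.49 | 0.15 |

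**6. Every participant as a test case.** Fisher's formula at n = 40 gives 0.22 to 0.70 around r = 0.5. This is approximate, because cross-validation folds share training data. In R² it is 0.22² = 0.05 to 0.70² = 0.49.

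**The case against.** The strongest reply is that this is a condensed article. It describes supervised learning in general terms, and the metric, number of splits and unit of splitting may be in a fuller document. That stands for those details: their absence alone would be no finding. A reader might infer that the plan commits to exactly one split. The wording makes that the natural reading, but it does not state it or rule out repeated division.

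Four further limits stand.

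- A reader might infer that a network which only relearned baseline severity would confirm Hypothesis 4. The article does not support that. The hypothesis is a prediction, no criterion fixes what confirms it, and a baseline-only model passes a correlation of 0.5 in only 53-55% of simulated splits. It could look predictive; it need not.
- Whether symptom scores are inputs is unsettled, because the data-collection section's predictor list omits them.
- The correlation of 0.5 is a planning value for clinician-rated PTSD at two time points, not an estimate for every outcome and follow-up visit.
- The aim is exploratory, and the Discussion introduces the prognostic models as a hope.

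A final objection is that cross-validation does not remove the limit set by 40 people: the interval in step 6 still spans the 0.25 benchmark. That is correct and belongs in the plan. It does not favour the described approach, which is less precise and compares with nothing. The lack of a comparator matters however many splits are made.

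**Conclusion.** The concern holds in a limited form. The article sets a prediction of accuracy beside a training/testing division of data from at most 40 people, with no benchmark. Under an assumed 20-30% hold-out by person, the resulting figure is close to uninformative: a true correlation of 0.5 may appear as anything from roughly -0.3 to 0.9, and pure noise reaches 0.5 in 5-10% of splits. If symptom scores enter the model, baseline severity alone could account for R² of 0.25 at the planning correlation. Over r of 0.3 to 0.7 the range is 0.09-0.49 for the endpoint score or 0.35-0.15 for the change score.

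These sizes rest on the assumed hold-out fraction, equal variances and the reading as one hold-out. The absence of a comparator rests on none of them. The change is worth making before the final analysis; the article reports 11 patients through the intervention so far.

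**What to change.** In the Data Analysis section for Objective 4:

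- State that performance will be estimated by repeated, nested cross-validation divided by participant. Everyone then serves as a test case, and no person's sessions fall on both sides of a division.
- Evaluate a regression on the baseline score alone in the same folds. Table 1 already schedules CAPS-5 at week 1 for both groups, so no new measurement is needed.
- Report the difference in held-out error between network and benchmark, with an interval.
- Treat Hypothesis 4 as supported only if the network improves on the benchmark. Otherwise report the models as exploratory and soften the Discussion's statement about individual clinical decisions.
- State whether symptom scores are inputs, so that the two Objective 4 sections agree.

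The cost is more computing, a paragraph of text and a stricter bar for Hypothesis 4. No visit, measure or participant burden changes. With 40 people the comparison may remain inconclusive, and the plan should say so in advance.
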